## Design

This is a 4-year, two-center, randomized controlled trial, that is single-blind (participants [Pps]) and uses a stratified sample block design with repeated measures. We are comparing the SystemCHANGE™ intervention to the attention control intervention in adult kidney transplant recipients with existing medication nonadherence documented by electronic monitoring. The repeated-measures design provides longitudinal data regarding medication nonadherence which allows us to determine when the intervention becomes effective (to determine if a lower dose of SystemCHANGE™, e.g. shorter time of delivery, is possible). It also allows us to track possible decay in medication nonadherence over time following the intervention.

We are examining the experimental effect on the outcome variable MA. During the 3-month screening phase, all Pps are using electronic monitoring to document medication taking. Those who are adherent (MA rate of .85 % or greater) exit the study. To prevent the “ceiling” effect, those with documented medication nonadherence (MA rate of less than .85 %) are stratified by low (<70 %), and moderate (70-84 %) nonadherence, based upon our previous medication nonadherence pattern research [41]. They then enter the intervention phase of the study and are randomized into either the treatment (SystemCHANGE™ intervention) or the attention control group (attention control condition). During the 6-month intervention phase, all Pps receive a home visit at baseline plus six telephone calls (at intervention months 1, 2, 3, 4, 5, 6). In addition, Pps randomized into the SystemCHANGE™ intervention are also guided in implementing SystemCHANGE™ activities related to medication taking by the Research Assistant (RA). Control group Pps receive RA-provided education guided by healthy living patient educational materials. The maintenance phase begins after the intervention and runs for an additional 6 months. This phase examines how Pps maintain MA in the absence of an intervention; however, we are continuing to use electronic monitoring to measure the outcome variable. Health outcome and healthcare cost data are collected during the intervention and maintenance phases.

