### Statistical analysis

Sample size and power calculations are based on comparing expected change in medication adherence rate of patients in each group at six months - an expected adherence mean difference of 10 % based on our pilot study findings and the literature. We use an alpha of .05 and provide for 90 % power to detect indicated effect sizes in this two-arm randomized study. An effect size difference of 70 % is based on a conservative estimate of our pilot work. A sample size of 46 older KT recipients per group (final total sample 92) will meet these assumptions and provide sufficient power. Recruitment and retention rates are calculated from our pilot study, other adherence studies at the same sites, and are documented in one similar RCT adherence study in older KT recipients [63, 64]. We selected an adherence rate of 85 % to divide the adherers from the non-adherers based upon our preliminary work describing 4 clusters of KT medication adherers: those who (1) take medications on time (1.0-.85 MA rate), (2) take medications on time with late/missed doses (.84-.70 MA rate), (3) rarely take medications on time and who were late with morning and/or evening doses (.69-.20 MA rate), and (4) missed many doses (<.20). Even minor deviations in dosing adherence lead to poor outcomes, though no studies have determined the criterion adherence “dose” that distinguishes good and poor outcomes.

Appropriate descriptive analyses will be performed to examine distributional characteristics for collected measures, as well as to summarize changes over time as a function of group assignment. During this initial phase, we will explore bivariate relationships among primary and secondary outcome measures and variables thought to affect medication adherence. In addition, we will conduct analyses to determine whether the randomly assigned groups are equivalent at the start of the study on the demographic and other measures collected at baseline. Before hypothesis-testing analyses are conducted, exploratory analyses will be performed to examine the effect of various mediators and moderators on the relationship between intervention, adherence, and clinical outcome. The results of these analyses will determine what additional variables will be incorporated in the subsequent hypothesis testing (e.g., analysis of covariance).

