Our primary analysis assesses whether the SystemCHANGE™ intervention is more effective than the attention-control intervention in increasing MA in adult kidney transplant recipients at the completion of the 6-month intervention and 6-month maintenance phases. We hypothesize that adult kidney transplant recipients receiving the SystemCHANGE™ intervention will have higher immunosuppressive MA rates than the attention-control group at the completion of intervention and maintenance phases. Since rate responses will most likely violate the normality assumption, the non-parametric method, Mann- Whitney test, will be used for comparing the two groups. However if the normal assumption is satisfied through transformation or as raw data measures, t-test will be applied for group comparison. Possible covariates resulting from demographic data and screening phase MA will be included in the analysis to adjust for possible bias.

Our secondary analysis assesses the MA patterns in both the SystemCHANGE™ and attention-control groups. Specifically we are interested in determining when the intervention becomes effective (e.g., what “dose” is needed) and the pattern of decay in MA over time in both groups. The dependent variable for these research questions are the repeated measurements of immunosuppressive MA rates at 12 time points [i.e. 1, 2, 3, 4, 5, 6, 7, 8, 9, 10, 11 and 12 months] and the independent variable is group assignment and time effect. Poisson regression analysis will be used for these questions. Proc Nlmixed procedure in SAS will be used for Poisson regression modeling. In order to answer the hypothesis we will test for group-by-time interaction to test if the two groups have different time profiles for MA or not. Possible covariates resulting from demographic data and screening phase MA will be included in the model to adjust for possible bias. Repeated measures from the same Pp will be accounted for using a random effect in the model.

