Our third exploratory aim is to determine if the SystemCHANGE™ intervention is cost-effective. Our hypothesis is the cost for the SystemCHANGE™ intervention will be less than the cost for the attention-control intervention. To determine the cost-effectiveness of the SystemCHANGE™ intervention compared to the attention-control intervention, both intervention and resource use costs will be evaluated and compared to MA change. A cost-effectiveness analysis will be performed at the end of the intervention period and again at the end of the maintenance period. If there is no treatment effect, a cost-analysis will not be performed. The analysis performed at the end of the maintenance period will be cumulative, incorporating costs and benefits incurred throughout the project. A cost-effectiveness analysis, performed at the end of the maintenance period (calculated for both the intervention and maintenance periods), will evaluate both intervention and control, and resource use costs which will be compared to adherence change. The sum of the total intervention and control costs and resource use costs will be the numerators for testing this hypothesis. The change in adherence (from baseline to end of intervention [or end of maintenance] period) will be the denominator. We will identify all direct intervention costs related to the intervention and the control (planning, designing, and implementation of each intervention, personnel, supplies, travel, and equipment). We will identify resource use costs (hospitalizations, clinic, observation, and ER visits) for both groups. Resource use costs will be obtained from publically available data, e.g. Hospital Compare, Hospital Stats, H-CUP. The DRG will be obtained with a conversion rate and then adjusted by hospital specific information, e.g. academic, location.

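### The adherence-based cost-effectiveness ratio at the end of maintenance is called cumulative in costs and benefits, but its denominator is a baseline-to-end change that leaves out earlier benefit since lost

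*Protocol article*

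**What the plan says.** All the key text is in the protocol article, Statistical analysis, in the paragraph on the third exploratory aim. Cost-effectiveness is assessed at the end of the intervention and again at the end of maintenance. On the second analysis the article states: "The analysis performed at the end of the maintenance period will be cumulative, incorporating costs and benefits incurred throughout the project". It adds that this analysis is "performed at the end of the maintenance period (calculated for both the intervention and maintenance periods").

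The ratio is then defined. For the top: "The sum of the total intervention and control costs and resource use costs will be the numerators for testing this hypothesis". For the bottom: "The change in adherence (from baseline to end of intervention [or end of maintenance] period) will be the denominator". The paragraph also rules out a cost analysis if there is no treatment effect, without naming the time point at which that is judged.

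Three other places bear on the point:
- Design: "The maintenance phase begins after the intervention and runs for an additional 6 months", with no intervention delivered in that time.
- Statistical analysis, secondary analysis: one question is "the pattern of decay in MA over time in both groups", and the data are "repeated measurements of immunosuppressive MA rates at 12 time points", months 1 to 12.
- Cost-effectiveness: the primary cost-effectiveness endpoint is an ICER per QALY, with the quality weight multiplied by the days in the observational period.

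**The concern.** The principle and the formula in this paragraph cannot both be followed. A cumulative benefit counts every month in which adherence was better. A change from baseline to the end of a period counts only where patients finish. The numerator covers 12 months of intervention and resource-use cost, and the denominator covers the state at the close.

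This matters most if the effect fades once contact stops, which is the question the maintenance phase was built to answer. A programme that improved adherence for most of a year and then lost ground would be charged its full cost and credited only with the remainder. The 6-month and 12-month ratios would also be hard to compare, because the second can worsen through decay alone even when total benefit has grown. Two analysts, one following the cumulative sentence and one following the formula, could report materially different ratios from the same data.

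**Working it through.** The article gives no cost, ratio or decay figure, so there is nothing to reproduce. The check compares the stated denominator with a cumulative one in an illustration.

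**Inputs**
- From the article (Statistical analysis, sample size): "an expected adherence mean difference of 10" per cent between arms at six months.
- From the article: 6 months of intervention, 6 of maintenance, and monthly adherence values at months 1 to 12.
- Assumed: the 10-point gain is present from month 1 and constant through month 6.
- Assumed: linear decay over months 7 to 12 to a gain of g points at month 12.
- Cost is the same under both rules and cancels.

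**Formulas**
- Months 1-6: 6 × 10 = 60 point-months.
- Months 7-12: sum over k = 1..6 of 10 + (g − 10)k/6 = 60 + 3.5(g − 10).
- Total over 12 months: 120 + 3.5(g − 10). The mean gain is this total divided by 12.
- Factor by which the stated rule exceeds cost per point of 12-month mean gain: mean gain ÷ g.

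**Results**

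| Gain at month 12 (g) | Total point-months | 12-month mean gain | Mean ÷ g |
|---|---|---|---|
| 10 (no decay) | 120.00 | 10.00 | 1.00 |
| 7.5 | 111.25 | 9.27 | 1.24 |
| 5 | 102.50 | 8.54 | 1.71 |
| 2.5 | 93.75 | 7.81 | 3.12 |
| 0 | 85.00 | 7.08 | undefined |

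In the last row 85 point-months have been gained, yet the stated ratio does not exist.

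**Softer reading.** Suppose the end of maintenance means adherence averaged over the maintenance phase. With g = 5 that average is 42.5/6 = 7.08, against a 12-month mean of 8.54, a factor of 8.54/7.08 = 1.21. The distortion is smaller but remains, because months 1-6 are still left out.

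**Comparing the two planned analyses.** Take g = 5 and, for illustration, no added cost in maintenance. The stated denominator falls from 10 to 5, so the ratio doubles between the 6-month and 12-month analyses. On a cumulative scale the denominator rises from 60 to 102.5 point-months, so the ratio falls to 60/102.5 = 0.59 of its 6-month value. The two rules move in opposite directions.

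**The case against.** The strongest reply is that cost per point still held at the end of follow-up is a legitimate quantity. It matches the primary aim, which compares adherence at completion of each phase, so calling it an overstatement presumes that the cumulative measure is the right one. That would carry weight if the article had not itself described this analysis as cumulative in benefits. The end-of-period ratio may be reported, but not under that description.

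Several stronger readings are tempting and are not supported:
- *That the trial expects the effect to decay.* The Design section speaks only of possible decay, and decay is examined in both groups, which need not shrink the difference between them. The hypothesis is that adherence is still higher at the end of maintenance.
- *That the protocol projects a 10-point gain throughout months 1-6.* The figure is given at six months; constancy from month 1 is an assumption here.
- *That the 6-month ratio is likewise distorted by slow onset.* The Discussion says the pilot suggests an immediate effect, so this cannot be pressed.
- *That the error is many-fold.* A factor of 7.4 (mean 7.38 against 1 point left) needs 90% of the gain to be lost.
- *That the trial's cost-effectiveness conclusion as a whole is affected.* The QALY-based ICER is weighted by time and does not drop early benefit in this way.

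The rule against a cost analysis without a treatment effect is a real guard, but a partial one. Judged at month 6, it leaves a near-zero 12-month denominator possible. Judged at month 12, it suppresses the analysis even though benefit was obtained earlier. It does nothing for small non-zero denominators.

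The averaging window for adherence could fairly be left to an analysis plan. The conflict does not depend on it, as the softer reading shows.

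**Conclusion.** The point stands as an internal contradiction confined to the adherence-based ratio of the third exploratory aim: benefits are called cumulative, and the denominator is not. If the between-arm gain decays in maintenance, the stated rule overstates cost per unit of adherence benefit, by about 1.2, 1.7 or 3.1 times for 7.5, 5 or 2.5 points remaining of 10. These factors rest on assumed shapes and are illustrations, not forecasts; if the gain is fully maintained there is no distortion. The primary adherence comparison is untouched. The wording should be settled before results are seen, because the choice of reading could otherwise be made after the decay is known.

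**What to change.** For the end-of-maintenance analysis, define the denominator as cumulative adherence gain over the interval in which costs are counted: the sum (or area under the curve) of monthly adherence changes from baseline over months 1-12, compared between arms and expressed in adherence-point-months. Use the same definition over months 1-6 for the first analysis, so that the two are on one scale. It should be a sum and not a mean: a constant 10-point gain has mean 10 in both analyses but gives 60 and 120 point-months, so a mean would not be cumulative.

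The baseline-to-end change can be kept as a secondary ratio, labelled as cost per point retained at the end of follow-up. State also at which time point the no-treatment-effect rule is judged.

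The cost is wording only, since the 12 monthly values are already planned. The downside is that the ratio is then per adherence-point-month, a less familiar unit than a point of adherence at the end of a period.

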## Methods

### Aims

The primary aim of the trial is to determine whether the SystemCHANGE™ intervention is more effective than the attention control intervention in improving MA in adult kidney transplant recipients at the completion of the intervention and maintenance phases. We hypothesize adult kidney transplant recipients participating in the SystemCHANGE™ intervention will have higher immunosuppressive MA rates than those participating in the attention control at the completion of intervention and maintenance phases. A secondary aim is to examine the patterns of MA in this group. We will determine when the intervention becomes effective (e.g., what “dose” is needed) and what the pattern of decay in medication adherence is over time in both groups. Our exploratory aims are to determine whether the SystemCHANGE™ intervention is more effective than the attention control in decreasing poor health outcomes (e.g., infection, acute/chronic rejection, graft loss, death, and increasing creatinine/blood urea nitrogen,), to explore potential mediators (social support and systems-thinking) and moderators (ethnicity, perceive health and level of medication nonadherence) of MA, and to determine whether the SystemCHANGE™ intervention is cost-effective. We hypothesize patients in the SystemCHANGE™ intervention will demonstrate lower levels of poor outcomes than attention controls at 12 months. We also hypothesize the cost-effectiveness ratio for the SystemCHANGE™ intervention will be less than the cost-effective ratio for the attention-control intervention.

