### Cost-effectiveness

The primary endpoint of cost-effectiveness measures will be the incremental cost-effectiveness ratio (ICER) of the SystemCHANGE™ intervention relative to the attention-control, which assesses the incremental cost per health-related quality-adjusted life year gained. The perspective of cost-effectiveness is a third-party payer. A micro-costing approach will be used to measure the intervention’s resource use, based on a log of resource use for each intervention. The resources used for the delivery intervention in the interventional and the control group will be tracked over the study period. The Pps will track the type and quantity of medical services consumed (doctor’s office, clinic, hospital, medication). The unit cost of personnel time will be based on actual hourly salary rates and fringe benefits. Unit costs of each hospitalization, ER visit, clinic visit, and physician fee will be estimated based on Medicare’s average reimbursement rate. The unit cost of medication will be estimated from the average wholesale price plus the dispensation fee of 2 %. To determine the number of quality-adjusted life years over the observational period, the weight will be multiplied by the number of days in the observational period. All cost measures will be adjusted to the constant U.S. dollar. Sensitivity analyses will examine key parameters that may affect ICERs.

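### The exploratory cost-effectiveness analysis is specified inconsistently: two denominators, two hypotheses that the same data can split, and a condition that can leave costs unreported

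*Protocol article*

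**What the plan says.** Three sections of the protocol article define this analysis.

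- **Cost-effectiveness.** The primary endpoint is an ICER of SystemCHANGE relative to the attention control, "which assesses the incremental cost per health-related quality-adjusted life year gained", from a third-party payer perspective.
- **Statistical analysis, third exploratory aim.** The ratio is built differently: "The sum of the total intervention and control costs and resource use costs will be the numerators for testing this hypothesis", and "The change in adherence (from baseline to end of intervention [or end of maintenance] period) will be the denominator". Neither QALYs nor an ICER appears there. Analyses are planned at the end of the intervention period and, cumulatively, at the end of maintenance.
- **Hypotheses.** The Aims state: "We also hypothesize the cost-effectiveness ratio for the SystemCHANGE™ intervention will be less than the cost-effective ratio for the attention-control intervention". The Statistical analysis section states: "Our hypothesis is the cost for the SystemCHANGE™ intervention will be less than the cost for the attention-control intervention".
- **Condition.** The Statistical analysis section adds: "If there is no treatment effect, a cost-analysis will not be performed". It does not say what counts as no effect, or at which time point.

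On the source of QALYs, Table 2 schedules no quality-of-life measure. The Additional outcomes section does list health-related quality of life among the outcomes collected for all three phases.

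**The concern.** Each section presents its version as the analysis, and none is ranked above the others. An analyst who follows the Aims, one who follows the Cost-effectiveness section and one who follows the Statistical analysis section would compute different quantities and could draw opposite conclusions. The choice could then be made after the data are seen.

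The contrast in the Aims is also a poor one. One ratio per arm, cost over that arm's own change, is an average ratio. It does not measure what an extra unit of benefit costs when one programme replaces the other. Its denominator includes change that neither programme caused, because everyone was selected for low adherence at screening and regression to the mean is expected.

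Finally, making the analysis conditional on an effect means that a cost difference may never be reported, although one of the two stated hypotheses concerns cost alone.

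**Working it through.** **Comparison of the text**

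| Element | Aims | Cost-effectiveness | Statistical analysis |
|---|---|---|---|
| Denominator | not named | QALYs | change in adherence from baseline |
| Contrast | ratio in one arm against ratio in the other | incremental, between arms | not stated; plural numerators suggest one ratio per arm |
| Hypothesis | lower ratio | none | lower cost |

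**Can the two hypotheses disagree?** The article gives no cost figures, so the inputs here are assumed: cost 3000 (SystemCHANGE) and 1500 (control), and a SystemCHANGE gain of 12 adherence points. The per-arm ratio is C/E. The incremental ratio is (C_I − C_C)/(E_I − E_C).

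| Control change | Ratio, SystemCHANGE | Ratio, control | Incremental ratio |
|---|---|---|---|
| +2 | 3000/12 = 250 | 1500/2 = 750 | 1500/10 = 150 |
| +0.1 | 250 | 1500/0.1 = 15000 | 1500/11.9 = 126 |
| −2 | 250 | 1500/(−2) = −750 | 1500/14 = 107 |

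In the first two rows the lower-ratio hypothesis is met and the lower-cost hypothesis fails. In the third row control adherence falls, yet the control ratio is numerically the smaller, so the ordering has no meaning. The incremental ratio stays interpretable in all three.

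**How likely is an unusable control ratio?** The article gives no figure for this. The inputs come from its sample size statement: a 10-point difference, an effect size of 70% read as d = 0.7, and 46 per group. That reading reproduces the stated size: a two-sided t-test at alpha 0.05 and 90% power needs 43.87 per group, and 43.87/(3/π) = 45.94, or 46, with the Mann-Whitney efficiency.

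- Implied SD = 10/0.7 = 14.3 points. I assume that the SD of change equals this.
- SE of the control mean change = 14.3/√46 = 2.11.
- P(mean change ≤ 0) = Φ(−true change/2.11) = 0.50 at 0 points, 0.17 at 2 and 0.01 at 5.

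**What does the condition do?** I assume that no effect means p ≥ 0.05, two-sided, at 46 per group.

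- Probability that the analysis is skipped: 8.7% at d = 0.7, 34% at 0.5, 70% at 0.3.
- Mean overestimate of the effect when it is significant: the true z is d·√(46/2), which is 3.36 at d = 0.7. The mean z given z > 1.96 is 3.36 + φ(1.40)/Φ(1.40) = 3.36 + 0.16 = 3.52, a ratio of 1.05. The same formula gives about 1.23 at d = 0.5 and 1.59 at d = 0.35.

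**The case against.** Several points on the other side are sound.

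- **The incremental ratio in the Cost-effectiveness section is a valid estimand.** A reader might infer that the plan cannot give any valid answer. The article does not support that: followed alone, this definition would serve. Cost per QALY and cost per adherence point can also both be reported if ranked. The fault is that they are not ranked or aligned.
- **A reader might infer from Table 2 that QALYs have no source.** The Additional outcomes section lists health-related quality of life for all three phases. What remains is a mismatch between that section and Table 2. An article may leave the name of the instrument to the full protocol.
- **The per-arm reading is only partly explicit.** The Aims compare two ratios but name no denominator; the Statistical analysis section names a denominator but not how the arms are compared. The combination is an inference, though a natural one.
- **The control-ratio risk depends on assumptions.** It matters only if control adherence moves little. Regression to the mean after selection would tend to push it up, towards the 1% case.
- **A between-arm ratio has the same weakness.** Its denominator has SE 14.3·√(2/46) = 2.98, so at true differences of 2 to 0 points it is zero or negative with probability about 25% to 50%. This stands, and it is why the remedy needs net benefit or the cost-effectiveness plane, not a bare ratio.
- **No cost data are discarded.** The Design section collects them in both phases regardless. Only the analysis is omitted.

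**Conclusion.** The concern holds as a matter of inconsistent specification. The conflicts over denominator and hypothesis, and the condition on running the analysis, are in the current text and need no assumption. Following the sections literally can give opposite conclusions from the same data, and a comparison of per-arm average ratios is not a valid cost-effectiveness contrast.

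The sizes are conditional. The 250, 750 and 150 figures illustrate a conflict under assumed costs and gains; they are not forecasts. The probabilities of 0.50, 0.17 and 0.01 rest on an assumed SD of change of 14.3 points and on the true control change. The overestimate of about 5% holds at the design effect if the condition means p < 0.05; larger values apply only if the true effect is smaller.

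The aim is exploratory, and the primary adherence comparison is unaffected. The change should be made, but it does not threaten the main result.

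**What to change.** 1. In the Aims, Cost-effectiveness and Statistical analysis sections, name one primary between-arm estimand: difference in mean cost over difference in mean effect. Choose either the baseline-adjusted adherence difference or QALYs as the single primary denominator, and make the other secondary.
2. Keep both planned time points, with the cumulative 12-month analysis as primary.
3. Replace the per-arm ratio hypothesis and the lower-cost hypothesis with one statement about that estimand.
4. Report joint uncertainty in cost and effect by incremental net benefit, or by bootstrap on the cost-effectiveness plane. Both stay usable when the effect difference is near zero.
5. Delete the condition, so that the analysis is run and reported whatever the adherence result.
6. Reconcile Table 2 with the Additional outcomes section on quality of life, and keep the QALY ratio only if the measure collected yields utility weights.

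The cost is rewording and a modest amount of analysis. No extra participants are needed. New data collection would arise only if QALYs are kept and the present quality-of-life measure does not give utilities.
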